**Methods:**

We used a theory-based and human-centered design (HCD) to adapt an already piloted software to design “Call for life-TB” (CFL-TB), an MHI that utilizes IVRT to deliver adherence and appointment reminders and allows remote symptom reporting. This open-label, multicenter, randomized controlled trial (RCT), with nested qualitative and economic evaluation studies, will determine the impact of CFL-TB on TB treatment success in patients with drug-susceptible TB in Uganda. Participants (*n* = 274) at the five study sites will be randomized (1:1 ratio) to either control (standard of care) or intervention (adherence and appointment reminders, and health tips) arms. Multivariable regression models will be used to compare treatment success, adherence to treatment and clinic appointments, and treatment completion at 6 months post-enrolment. Additionally, we will determine the cost-effectiveness, acceptability, and perceptions of stakeholders. The study received national ethical approval and was conducted in accordance with the international ethical guidelines.

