### Control arm and the standard of TB care in Uganda

The standard of care at all TB treatment centers follows the national TB treatment guidelines [40]. The standard treatment duration is 6 months, except for patients with TB meningitis and osteoarticular TB who require 12 months of treatment. The standard regimen and duration of treatment for patients with drug-susceptible TB are 2 months for isoniazid, ethambutol, rifampicin, and pyrazinamide, followed by four months of rifampicin and isoniazid [34]. Patients are reviewed every 2 weeks for the first month and monthly thereafter. All patients are encouraged to register a close household or community member to directly observe therapy, but this is not enforced. Patients receive health education during clinic visits with messaging on adherence and treatment completion. At treatment initiation, patients are routinely encouraged to adhere to treatment and appointments, but there are often no patient support systems provided to enhance this. Some patients may use other reminder systems of their choice [41] but this has not been described in patients with TB.

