### Description of the proposed mobile health intervention

The technology to be evaluated in this study is Call for Life-TB (CFL-TB^TM)^, a software that is based on open-source mobile technology for community health (MoTeCH) [42]. MoTeCH was initially developed by the Grameen Foundation and the University of Southern Maine with the support of Janssen, the Pharmaceutical Companies of Johnson and Johnson. It was designed as a community MHI platform to improve treatment compliance in patients in LMICs [42, 43]. We then adapted and evaluated the technology to support people living with HIV in Uganda and named it Call for Life ^TM^ (CFL) [34]. CFL-TB uses interactive voice response (IVR) or short messaging service (SMS) to communicate with PLHIV via mobile phones [34]. This prototype, “Call for Life-Uganda”, was iteratively adapted to design CFL-TB, a technology tailored to address the needs of patients with TB. The needs of patients with TB were enumerated through discussions with health workers and patients at IDI HIV/TB clinics. The software was sequentially upgraded, and the subsequent versions were reviewed by end-users at each stage. End-users (study staff and patients with TB) reviewed the software for suitability and suggested changes. Overall, the changes were aimed at optimizing the usability and security of the software. Participants in the intervention arm will receive standard of care plus CFL-TB enhanced TB care, and those in the control arm will receive standard of care.

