### The intervention (CFL-TB)

CFL-TB delivers once-daily adherence reminders, pre-appointment reminders, and targeted educative behavior change messages and allows patients to report symptoms to health care workers (HCWs) remotely. As advised by Iribarren et al., participants will decide their preferred language and the timing and frequency of reminders and will ensure that the content is culturally sensitive [44]. The software also delivers calls to registered care providers (buddies) of patients to facilitate daily observed therapy (DOTS), in line with the World Health Organization and Ministry of Health guidelines [14, 40]*.* In Uganda, daily reminders are generally preferred by patients over weekly reminders [8]. To increase adherence to the intervention, if the first call is not answered, the system will make two additional calls, 15 min apart. The study staff will also interview participants in the intervention arm to determine whether they are experiencing any problems. Health care workers enroll patients in the system, monitor the delivery message delivery of messages, and provide ongoing technical support, such as setting personal identification numbers (PINs) and swapping the registered telephone numbers. In contrast, participants are responsible for making and receiving calls. We will synchronize appointment reminders with scheduled appointments, and the software will initiate a call before and on the day of the clinic review. Participants select their preferred time to receive the reminder calls and set their PIN. The system offers short educational messages to increase knowledge about TB/HIV and general health [40]. The CFL-TB software is interoperable with other health information systems used in Uganda, including DHIS2, a web-based database for health reporting.

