### Trial endpoints

The primary endpoint is treatment success (at 6 months): treatment success is a composite outcome, comprising treatment completion and cure in patients with clinically and bacteriologically diagnosed TB, respectively. It is a robust and agreed indicator of treatment success in TB programs. In patients with bacteriologically diagnosed TB, cure is defined as having a negative sputum test in the last month of treatment and on at least one previous occasion [47]. For clinically diagnosed patients, completion entails 6 months of therapy. The denominator for each arm will be the number of patients enrolled. At the same time, the numerator is the sum of bacteriologically and clinically diagnosed patients with cure or treatment completion, respectively.

This RCT also has several secondary endpoints. First, we will determine the TB cure rates in patients with microbiologically diagnosed TB. Second, we will determine treatment completion for patients clinically diagnosed with TB in the two arms: Third, retention rates will be determined and compared between the study arms. Patients will be deemed to be actively engaged in care if they attend a clinic visit within one month of a scheduled appointment. Additionally, we will compare appointments. We will categorize visits as “early,” if they present before an appointment, “prompt” if they show up within three days after the appointment date, “late” if they present after three days but within 30 days of a scheduled appointment and missed if patients do not show up at all or present after 30 days. Fourth, we will determine the incremental costs per additional DALY averted per percentage point increase in treatment success in the intervention versus the control arm. In addition, we will compare adherence rates at months 2 and 6. Depending on the availability of drug susceptibility tests, we will compare the rates of MDR-TB. To understand the impact of the intervention on the treatment outcomes and the potential for adoption and scaling of the intervention, we will explore the perceptions and experiences of patients and care providers towards the MHI. Finally, we will determine the uptake and adherence to the intervention. We will consider the successful receipt of a reminder as a proxy for the utilization of the technology. Therefore, we will determine the proportion of successful calls in the intervention and control arms.

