### Analysis of endpoints

The planned analyses are summarized in Table 2. We will use a two-tailed *p* value of 0.05 and report the 95% confidence intervals for all endpoints. In all analyses, we will control for confounders of adherence and retention [7, 48, 49]. In both primary and secondary outcomes, we will undertake per-protocol and intention-to-treat analyses.

**Table 2 Tab2:** Analysis of quantitative outcomes

Outcomes	Measure of outcomes (intervention versus control arm)	Statistical analysis
Treatment success	Proportion of patients with treatment success at six months. Odds ratio of treatment success	Logistic regression, odds ratios
Cure rates	Proportion of patients cured of TB; odds ratio of TB cure	Logistic regression, odds ratios
Treatment completion	Treatment completion rate; odds ratio of treatment completion	Logistic regression, odds ratios
Retention in care	Hazards of attrition in the intervention versus control; Cumulative attrition at six months	Cox’s proportional hazards model, log-rank test
Adherence to TB medicines	Mean adherence rates (proportion of TB medicines)	Mann-Whitney U test and Poisson regression
Appointment keeping and punctuality	Proportion of patients who keep an appointment; Proportion of patients with early, prompt, and late visits	Ordered logistic regression
Drug-resistant TB rates	Proportion of patients with rifampicin-resistant TB	Logistic regression, odds ratios
Call success rates (2,4, and 6 months)	Proportion of successful calls	*t* test

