### Analysis of the primary endpoint

We will use logistic regression to determine the crude and adjusted odds ratios of treatment success in the intervention arm versus the control arm. The multivariable model will adjust just for potential confounders, including age, sex, employment status, bacterial load at baseline, TB category, and HIV status [7, 48, 49]. The stepwise backward elimination method will be used to fit the final model. The model with the lowest Akaike information criterion (AIC) statistic will be considered the best fitting. Covariates with a global/trend *p* value > 0.2 at the bivariate analysis, will be adjusted for in the final multivariate model. We will explore factor interactions, including the interaction between age adherence and sputum smear results at baseline. Where interaction is confirmed, we report both the main and interaction effects.

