### Sensitivity analysis

To determine the impact of nonadherence to the study intervention, we will stratify the analysis by utilization of the CFL-TB tool. For both primary and secondary quantitative endpoints, we will conduct an overall and stratified analysis by HIV status, TB type (pulmonary versus other forms of TB), and gender.

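### Call success is to be compared with a control arm that receives no calls, and outcomes are to be stratified by tool use, which is undefined in controls

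*Protocol article*

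**What the plan says.** **Who receives calls.** The abstract defines the arms as "either control (standard of care) or intervention (adherence and appointment reminders, and health tips) arms". The description of the intervention says that "those in the control arm will receive standard of care", and the next section that "CFL-TB delivers once-daily adherence reminders, pre-appointment reminders, and targeted educative behavior change messages". Of adherence and appointment keeping under standard care, the article says that "there are often no patient support systems provided to enhance this". No calls to controls are described.

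**Call success.** Trial endpoints uses successful receipt of a reminder as a proxy for use of the technology and continues: "Therefore, we will determine the proportion of successful calls in the intervention and control arms". Table 2 (Analysis of endpoints) has a row "Call success rates (2,4, and 6 months", measured as the proportion of successful calls and analysed by t test. The column heading above that row specifies intervention versus control. Analysis of quantitative endpoints describes the same measure at the same three times as a proxy for uptake and fidelity, with no test between arms.

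**Stratification.** To address non-adherence to the intervention, the Sensitivity analysis section states: "we will stratify the analysis by utilization of the CFL-TB tool". The same paragraph plans strata by HIV status, TB type and gender for the primary and secondary quantitative endpoints.

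**The concern.** Two stated analyses use tool utilisation as if it existed in both arms.

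The first cannot be carried out as written. If someone made it run by coding controls as zero, it would only confirm who was allocated to the tool.

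The second can be carried out, and that makes it the more important of the two. Utilisation is a behaviour that follows randomisation. Unlike HIV status, TB type or gender, it does not define a subgroup of controls. Patients who answer calls may differ in prognosis from those who do not, so a difference between users and controls mixes any effect of the tool with that selection. The trial aims to inform TB policy, and an apparent benefit in users could be used to explain away a null main result.

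**Working it through.** **1. Call success between arms**

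- Intervention arm: the proportion is successful calls divided by calls made.
- Control arm: no CFL-TB calls are made, so the proportion is 0/0.
- A two-sample t test with the control values missing returns no result.
- With controls set to zero and made-up intervention values (137 draws from a beta(6, 4) distribution), it returns t = 49.4 and p of about 7 × 10⁻¹³⁸. That restates the allocation and says nothing about uptake.

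Trial endpoints and Table 2 therefore conflict with the arm definitions and with Analysis of quantitative endpoints, where the measure is descriptive.

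**2. Which contrasts stratification by use allows**

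- Users versus all controls: a self-selected part of one arm against the whole of the other.
- Non-users versus all controls: the same problem in the other direction.
- Users versus non-users within the intervention arm: an observational comparison.

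None compares groups formed by randomisation. Covariate adjustment removes only the confounding that the covariates measure.

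**3. Illustration of the size**

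The documents give no utilisation rate, control success rate or link between use and prognosis, so all three are assumed here. From the plan come 137 per arm and the two-sided 0.05 level. Assumed are 70% success in both arms, no effect of the tool, a share *u* of users, and a gap *d* in underlying success between users and non-users.

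- Success in users = 0.70 + (1 − *u*)·*d*
- Success in non-users = 0.70 − *u*·*d*

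Example with *u* = 0.5 and *d* = 0.20: users 0.70 + 0.5 × 0.20 = 0.80; non-users 0.70 − 0.5 × 0.20 = 0.60. The spurious differences from controls are +10 and −10 points. The odds ratio for users is (0.80/0.20)/(0.70/0.30) = 1.71.

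Rejection rates come from 20,000 simulated trials with a pooled two-proportion z test. Paired entries are users / non-users, each against all controls.

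| *u* | *d* (points) | Difference (points) | Odds ratio | Rejects at 0.05 |
|---|---|---|---|---|
| 50% | 0 | 0 / 0 | 1.00 / 1.00 | 4.9% / 5.0% |
| 50% | 5 | +2.5 / −2.5 | 1.13 / 0.89 | 6.6% / 6.7% |
| 50% | 10 | +5 / −5 | 1.29 / 0.80 | 10.9% / 11.5% |
| 50% | 20 | +10 / −10 | 1.71 / 0.64 | 32.4% / 30.4% |
| 50% | 30 | +15 / −15 | 2.43 / 0.52 | 67.5% / 56.4% |
| 70% | 10 | +3 / −7 | 1.16 / 0.73 | 7.6% / 14.0% |
| 70% | 20 | +6 / −14 | 1.36 / 0.55 | 17.2% / 38.2% |
| 70% | 30 | +9 / −21 | 1.61 / 0.41 | 34.0% / 69.5% |

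A second simulation with no effect let one latent trait act on both uptake and success, with about 50% users. At a log odds ratio of 0.5 per SD it gave +2.5 and −2.3 points; at 1.0 it gave +7.7 and −7.6.

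**4. What an allocation-based estimate does in the same setting**

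Controls are not given the tool, so the complier effect is the intention-to-treat difference divided by the share of users. In the example, the intention-to-treat difference is 0.5 × 0.80 + 0.5 × 0.60 − 0.70 = 0, and 0/0.5 = 0. The selection cancels because whole arms are compared. The interval widens by about 1/*u*: 1/0.5 = 2 times with 50% users and 1/0.7 = 1.4 times with 70%.

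**The case against.** **The call-success error largely corrects itself.** A test without control data cannot produce a misleading estimate, and Analysis of quantitative endpoints already has the sensible version. This stands. That part is a matter of reconciling passages, but the wrong version appears both in the endpoint text and in Table 2.

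**The sensitivity sentence does not say that users are compared with controls.** This is true, and a description of outcomes by level of use within the intervention arm would also fit the wording. That reading is still observational, and the article does not label it so. The detail of how strata are formed may be in an analysis plan that is not shown. The choice of a stratification variable that controls cannot have is stated in the article.

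**A reader might infer that the analysis would show benefit in users and harm in non-users even if the tool did nothing.** The documents do not support this as a general statement. It requires use to track prognosis. The Discussion names power outages and sparse network signal as barriers, so missed calls need not reflect a patient's adherence. With a gap of 5 or 10 points and 50% users, a single trial would seldom reach significance (6.6% and 10.9% in the table).

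**A reader might extend the point to the primary model,** which explores interactions "including the interaction between age adherence and sputum smear results at baseline". That wording is garbled and exploratory, and adherence is not among the listed adjustment covariates. Adherence to TB medicines is also measured in both arms, unlike tool use. The same argument does not carry over, and this point does not rest on it.

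**The complier estimate has its own assumption.** Participants below a high threshold of use still get some calls, their treatment buddies are called, and health messages and symptom reporting are available. Allocation could then affect outcome without use as defined. This stands and shapes the fix.

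**Conclusion.** The point holds in two parts.

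- The between-arm test of call success contradicts the article's own description of the control arm and of the measure, and should be corrected. This needs no assumption.
- The stratification by utilisation yields non-randomised contrasts. They are biased to the extent that answering calls is related to prognosis. The size cannot be derived from the documents: illustratively about 2 to 15 points with 50% users, and zero if use is unrelated to prognosis. The upper figure reflects an assumed 30-point gap between users and non-users and is not a forecast.

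A reader might infer that the main conclusion of the trial is unsafe. It is not, on this ground: intention-to-treat analysis is kept, call success is a secondary measure, and the utilisation strata are labelled as sensitivity analysis. The change is worth making because it is cheap and because the stratified result could be misread.

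**What to change.** **Trial endpoints and Table 2.** Report call success at months 2, 4 and 6 in the intervention arm only, with confidence intervals that allow for repeated calls to the same participant. Remove the t test and any comparison with control, in line with Analysis of quantitative endpoints.

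**Sensitivity analysis.**

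- Estimate the effect of non-use by a complier average causal effect, with allocation as the instrument and use defined in advance.
- Preferably define use as any receipt of calls, and consider counting calls to the registered buddy. The exclusion restriction, that allocation acts on outcome only through use, is then more plausible than with a high threshold.
- State that assumption and the wider intervals.
- If strata by utilisation are still shown, label them as non-randomised and descriptive.

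**Cost.** Wording in two sections and one table row, plus one extra analysis from data already planned. The complier estimate is less precise than the intention-to-treat estimate. If nearly everyone receives some calls, the two will be close, and little will be learned about degrees of use.

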### Sample size determination

Based on results from a randomized controlled trial in Kenya that demonstrated a 9% increase in TB treatment success following the use of SMS [12], we hypothesize that the interactive voice response platform will lead to at least a 6% higher impact as compared to SMS reminder treatment success (i.e., a 15%-point difference compared to the control arm). A retrospective cross-sectional study of routine data on HIV/TB co-infected patients from the Uganda National Tuberculosis and Leprosy Program reported lost to follow-up rates of 3.5% and 16.6% in urban and rural settings, respectively [7]. The rate of lost-to-follow at the three TB clinics was approximately 11.8%. Therefore, assuming an 11.8% lost-to-follow-up rate, this study would require a minimum of 274 (137 patients per arm) patients to demonstrate a 15% increment in treatment success with a power of 0.8 and precision of 0.05.

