### Study hypothesis

We hypothesized that IVRT will have a 10% higher impact on treatment success than SMS intervention; therefore, we predict that CFL-TB will lead to a 15%-point increase in treatment success rate in the intervention arm compared to the standard of care (control arm). This is based on a previous RCT that reported 5–9% better treatment success in patients who received SMS adherence reminders versus the standard of care [12, 27].

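### The sample size allows for 11.8% loss to follow-up although the primary endpoint keeps every enrolled patient, so the stated power of 0.80 cannot be tied to that endpoint; the 15-point effect is also derived in two conflicting ways

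*Protocol article*

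**What the plan says.** The Sample size determination section of the protocol article gives the target as follows: "assuming an 11.8% lost-to-follow-up rate, this study would require a minimum of 274 (137 patients per arm) patients to demonstrate a 15% increment". The outcome is treatment success, and the stated power is 0.8 with a figure of 0.05 that the section calls precision. The Analysis of endpoints section fixes the test as two-sided: "We will use a two-tailed *p* value of 0.05". Neither a control-arm success rate nor a formula is given.

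The Trial endpoints section defines the primary endpoint on a different footing: "The denominator for each arm will be the number of patients enrolled". Its numerator holds only bacteriologically diagnosed patients who are cured and clinically diagnosed patients who complete treatment. The Analysis of endpoints section plans both intention-to-treat and per-protocol analyses.

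The 15 points appear in two sections. Under Study hypothesis: "We hypothesized that IVRT will have a 10% higher impact on treatment success than SMS intervention", with the SMS effect cited as 5 to 9%. Under Sample size determination, the cited SMS effect is 9% and the platform is expected to "lead to at least a 6% higher impact as compared to SMS reminder treatment success", which the section equates to a gain of 15 percentage points over control.

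**The concern.** Enlarging a sample for loss to follow-up is right when lost patients leave the analysis, because it restores the number analysed. Here they do not leave. A lost patient stays in the denominator and cannot enter the numerator, so loss changes the success rates and not the number analysed. Two cases follow:

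- If the planning rates already count losses as failures, no enlargement was needed.
- If they are rates among patients followed to the end, equal loss in both arms shrinks the difference, and the enlargement does not make up for that.

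The 0.80 is the figure against which a null result will be read. Readers need to know which endpoint, which scale and which control rate it belongs to. The two accounts of the 15 points also leave it unclear what gain over SMS the trial assumes.

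**Working it through.** **Inputs from the article.** Two-sided alpha 0.05 (taking the stated precision of 0.05 as alpha), power 0.80, difference 0.15, 1:1 allocation, loss 0.118, 137 per arm. **Not in the article:** the control success rate. It is assumed below and varied.

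**Formulas** (pooled-variance comparison of two proportions, with p̄ the mean of p1 and p2):

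- n per arm = [1.960·√(2p̄(1−p̄)) + 0.842·√(p1(1−p1)+p2(1−p2))]² / (p2−p1)²
- power = Φ{[(p2−p1)·√n − 1.960·√(2p̄(1−p̄))] / √(p1(1−p1)+p2(1−p2))}

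**1. Reproducing 137 per arm.** The stated inputs alone cannot give it, because the control rate is missing. More than one assumed rate fits:

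- Control 70%, with loss allowance: (1.157 + 0.489)² / 0.0225 = 120.5, and 120.5 / 0.882 = 136.6, so 137.
- Control 65%, no allowance: (1.238 + 0.524)² / 0.0225 = 137.9. At 65.5% it is 136.3.
- Other two-sided variants that include the allowance (unpooled variance, continuity correction, multiplying by 1.118) come within 3% of 274 at control rates of about 68 to 74%.

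The 274 therefore does not identify the control rate or prove how the allowance was used.

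**2. Power of 137 per arm on the endpoint as defined, assuming 70% control.**

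- *Rates apply to all enrolled:* 70% vs 85% gives Φ(1.03) = 0.848. Without enlargement, 121 per arm (242 in total) would already give 0.80.
- *Rates apply to those followed, 11.8% lost in each arm:* 0.70 × 0.882 = 0.617 and 0.85 × 0.882 = 0.750, a difference of 13.2 points, which gives Φ(0.398) = 0.655.

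**3. Range over the control rate, 15-point effect, 137 per arm.**

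| Control rate | Rates on all enrolled | Rates on those followed, 11.8% lost in each arm |
|---|---|---|
| 60% | 0.76 | 0.61 |
| 65% | 0.80 | 0.63 |
| 70% | 0.85 | 0.65 |
| 75% | 0.91 | 0.69 |
| 80% | 0.97 | 0.74 |

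**4. Sensitivity of the last column to equal loss.** Hold control at 0.617 (70% with 11.8% lost) and lower the loss in the intervention arm:

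| Intervention-arm loss | Intervention success, all enrolled | Power |
|---|---|---|
| 11.8% | 0.85 × 0.882 = 0.750 | 0.655 |
| 9% | 0.85 × 0.910 = 0.774 | 0.805 |
| 5.9% | 0.85 × 0.941 = 0.800 | 0.92 |

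**5. The 15 points.** Study hypothesis: 5 to 9 plus 10 gives 15 to 19, and reaches 15 only from the lower end of the SMS range. Sample size determination: 9 plus 6 gives 15. The increment over SMS is 10 in one section and 6 in the other. This comparison needs no assumption.

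**The case against.** The strongest reply is that every power figure above rests on a control rate the article does not give. The full protocol, listed as a supplementary file, may state it. That stands: the figures are conditional, and a condensed article may leave the rate to the full document.

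A reader might infer that the trial is underpowered, with true power near 0.65. The documents do not support this. The figure needs a control rate near 70%, a 15-point effect defined only among followed patients, and the same 11.8% loss in both arms. The intervention is meant to improve retention, which is itself a secondary objective, and a fall in intervention-arm loss to 9% brings power back to about 0.80. On the all-enrolled scale, which is the scale of the defined endpoint, 70% control gives more power than stated.

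A reader might also infer that 0.80 cannot be right on any reading. It can: at about 65% control on the all-enrolled scale, 137 per arm gives 0.80 with no allowance. In that case the 11.8% did no work, although the sample size text presents it as part of the reasoning.

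A loss allowance also has a legitimate use for the planned per-protocol analysis, but the text does not say that this is its purpose. Finally, both derivations end at 15 points, so the sample size is unaffected. That is correct, and it makes the conflict one of rationale.

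None of this reconciles a loss allowance with a denominator of all enrolled patients.

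**Conclusion.** The concern holds in conditional form. If the 11.8% allowance was applied, as the text implies, the 0.80 belongs to an analysis that drops lost patients and not to the primary endpoint as defined. If it was not applied, it should not appear in the justification. Either way the paragraph needs correcting.

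The direction of the error is not settled by the article. At an assumed 70% control, power is about 0.85 (rates on all enrolled) or about 0.65 (rates on those followed, equal loss). Only the second falls short of the stated figure, and it depends on the equal-loss assumption. The conflict between 10% and 6% over SMS is plain on the page but does not change the sample size.

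This is worth correcting at low cost. It does not put the design in doubt and is not a must-fix.

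**What to change.** Keep 274. In the Sample size determination section:

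- State the control success rate and the 15-point effect on the all-enrolled scale, with lost patients counted as not successful.
- Remove the 11.8% allowance, or say explicitly that it serves the per-protocol analysis.
- Restate the power that 137 per arm gives at the stated control rate, with a range over plausible rates.
- Do not insert 0.65 as the plan's power, since it rests on assumptions that the plan does not make.

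Use one derivation of the 15 points, with one SMS benchmark and one increment, in both Study hypothesis and Sample size determination. Adding the power at the cited 9-point SMS effect is optional.

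The cost is a reworded paragraph, one sentence under Study hypothesis and a short power table. No patients are added, and the endpoint and analysis do not change. The restated power may be higher or lower than 0.80.
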